### Aims, hypotheses, and study design

The present study is a randomized clinical trial aimed at generating evidence in support of the effectiveness of an online group psychological counseling intervention in university students with high levels of academic burnout. To this aim, the study design entails the comparison between students that will be randomly assigned to two matched groups: (1) a psychological counseling group (PC, *N* = 65) or (2) a waiting list control group (WL, *N* = 65). We will test the effect of time (pre-PC vs. post-PC) in interaction with the effect of group (PC vs. WL) on the score obtained in several self-report outcome measures, including scores on burnout symptoms, general wellbeing, and academic achievement as primary outcomes. We hypothesize that PC, compared to WL, should provide evidence of the efficacy of psychological counseling to decrease burnout symptoms and improve general wellbeing and academic achievement.

Moreover, to acquire data on possible mediators or psychological change, we will also assess a large set of secondary outcome variables potentially related to academic burnout, including effort-reward imbalances, basic psychological needs of satisfaction/frustration, intrapersonal and interpersonal emotion regulation, coping strategies and social support. Such variables will be directly and/or indirectly addressed in the psychological counseling sessions (see Section “Intervention” and Table 1). We hypothesize that secondary outcomes variables may be affected by the psychological counseling intervention, mediating or moderating its effects on primary outcomes.

**Table 1 T1:** Summary of psychological counseling intervention features.

**Session**	**Strategy**	**In-session activities**	**Treatment goals**	**TA techniques**
First	Psychoeducation	Information provision on stress, burnout, and coping Information provision about intervention action and goals	Self-awareness	Contract
	Agreement treatment goals	Set goals for time in treatment	Self-awareness	
	Promotion of social support	Introduction of participants and personal experiences sharing	Social support	Therapeutic alliance/group cohesion
Second	Psychoeducation	Information provision on psychological basic needs Identification of basic needs and their satisfaction or frustration in the academic context	Self-awareness	Strokes Therapeutic alliance/group cohesion

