### Statistical analysis

Descriptive statistics will be reported for participant recruitment, acceptance, adherence, and dropout rates. Baseline characteristics for each group will be reported to ensure group matching on these variables. To verify the reliability of the eight questionnaires, we will compute test-retest correlations between T1 and T2, and between T1 and T3 (using Pearson's *r* coefficients).

To assess the effects of PC on the outcome variables (MBI-SS, PGWB-S, and academic achievement), mixed model regressions will be utilized, by considering Time (T1, T2, and T3) and Group (PC vs. WL) as fixed factors and subjects as the random factor. This technique will allow us to test the interaction between Time and Group. Our expectation is that PC and WL should differ at T2 and T3, but not at T1, indicating that the PC group should achieve higher scores than the WL group after, but not before, the psychological counseling intervention.

A series of path analyses will be conducted to determine whether the measures obtained from the BPNSFS, ERI-SQ, CERQ-18, DIRE, Brief-Cope, and MSPSS questionnaires mediate the differences in the outcome variables between T1 and T2, and T1 and T3. For each analysis, the exogenous variables will be the outcome measures at T1, the mediators will be the scores in the subscales of the BPNSFS, ERI-SQ, CERQ-18, DIRE, Brief-Cope, and MSPSS questionnaires, and the endogenous variables will be the outcome measures at T1. Since each questionnaire involves multiple subscales, two separate models will be computed for each mediator. For example, for the BPNSFS questionnaire, we will test whether the Autonomy Satisfaction, Competence Satisfaction, Relatedness Satisfaction, Autonomy Frustration, Competence Frustration, and Relatedness Frustration subscales will mediate the associations between the T1 and T2 (or T1 and T3) outcome measures.

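### The mediation path models leave out Group, so they test how baseline scores carry over through a mediator and not how counseling works

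*Protocol article*

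**What the plan says.** Under Aims, hypotheses, and study design, the Protocol article expects that "secondary outcomes variables may be affected by the psychological counseling intervention, mediating or moderating its effects on primary outcomes". In causal order this is Group, then mediator, then outcome.

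The Statistical analysis section gives the purpose of the path analyses as finding out whether the subscales "mediate the differences in the outcome variables between T1 and T2, and T1 and T3". It then assigns the roles. "For each analysis, the exogenous variables will be the outcome measures at T1", the mediators are the subscale scores of the six secondary questionnaires, "and the endogenous variables will be the outcome measures at T1". The worked example, on the needs questionnaire, asks whether its six subscales "will mediate the associations between the T1 and T2 (or T1 and T3) outcome measures".

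Group (PC vs WL) is a factor in the mixed models in the preceding paragraph, which name burnout, wellbeing and academic achievement as outcomes. It is not mentioned in the path-analysis paragraph.

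**The concern.** A mediation analysis in a randomised trial asks whether assignment shifts the mediator and whether that shift accounts for some of the effect on the outcome. It therefore needs Group as the starting variable. The planned models start from the participant's own baseline score. Their indirect effect describes how much of the stability of an outcome over time runs through a correlated trait, and that can be large or small whether or not counseling works.

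Two errors could follow. A significant indirect path could be reported as a mechanism of counseling when counseling has no effect. A true mechanism could also go unseen, because the mediator moves with Group and not with the baseline score.

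**Working it through.** **Plan's own figure.** The article gives no figure for the mediation analysis. Its sample size does reproduce: with d = 0.50 and two-sided α = 0.05, the exact t-test power is 0.795 at 63 per arm and 0.801 at 64, so 64 per arm (128 in total) is correct. The present point does not touch it.

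**Where Group appears.**

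| Element | Hypothesis (Aims) | Path models (Statistical analysis) |
|---|---|---|
| Starting variable | Counseling, i.e. Group | Outcome at T1 |
| Mediator | Secondary variables | Subscales of the same questionnaires |
| Endpoint | Primary outcomes | Written as outcome at T1; purpose sentence and example imply T2 or T3 |

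The mismatch in the first row depends on no numerical assumption.

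**Size when counseling has no effect.** Inputs: n = 130 from the article. Assumed, because the article gives no correlations: T1-T2 outcome correlation 0.6; the mediator has the same correlation r with both outcomes; mediation is declared when both paths reach p < 0.05.

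- Path a (T1 outcome to mediator): z_a ≈ r√128 / √(1 − r²).
- Path b (mediator to later outcome, given the T1 outcome): partial correlation p = (r − 0.6r) / √[(1 − 0.36)(1 − r²)] = 0.5r / √(1 − r²), and z_b ≈ p√127 / √(1 − p²).
- Chance of declaring mediation ≈ Φ(z_a − 1.96) × Φ(z_b − 1.96).

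| r | z_a | p | z_b | Product | Simulation, one mediator |
|---|---|---|---|---|---|
| 0.2 | 2.31 | 0.102 | 1.16 | 0.637 × 0.211 = 0.13 | 13% |
| 0.3 | 3.56 | 0.157 | 1.79 | 0.945 × 0.434 = 0.41 | 40% |
| 0.4 | 4.94 | 0.218 | 2.52 | 0.999 × 0.712 = 0.71 | 70% |
| 0.5 | 6.53 | 0.289 | 3.40 | 1.000 × 0.925 = 0.93 | 92% |

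The worked example can be read as putting all subscales of a questionnaire into one model. With parallel mediators intercorrelated 0.4 (assumed), simulation gives these rates per subscale at r = 0.2, 0.3, 0.4 and 0.5:

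- three mediators: about 6%, 15%, 33% and 69%;
- six mediators: about 4%, 8%, 16% and 42%.

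The inflation needs both paths to be non-zero. If either is zero, the rate is at most about 5%. In a separate simulation with path coefficients set directly (T1 outcome to mediator 0.2 to 0.5, mediator to T2 outcome 0.2 to 0.4, direct T1-to-T2 path 0.5) and no counseling effect, a model with Group as the starting variable declared mediation in only about 4% to 6% of trials.

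**Size when counseling works through the mediator.** Assumed: Group shifts the mediator by 0.5 or 0.8 SD, mediator to T2 outcome 0.4, direct T1-to-T2 path 0.5, mediator unrelated to the T1 outcome, 65 per arm.

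- Without Group: path a is truly zero, so it is significant in about 5% of trials. Path b is almost always significant: residual SD √(1 − 0.25 − 0.16) = 0.77, SE ≈ 0.77/√130 = 0.067, z ≈ 5.9. Detection ≈ 0.05 × 1 = 5% (simulation 5.4% and 4.8%).
- With Group: SE of the shift = √(2/65) = 0.175, so z = 0.5/0.175 = 2.85 or 0.8/0.175 = 4.56. Detection ≈ Φ(0.89) = 0.81 or Φ(2.60) = 0.995 (simulation 82.5% and 99.6%).

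**The case against.** **The duplicated T1.** A reader might infer that the model cannot be estimated at all, since T1 is named as both predictor and endpoint. The article does not support that as the intended plan: the purpose sentence and the worked example in the same section both point to T2 and T3. It is a slip to correct, and correcting it leaves Group missing.

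**The Group effect on the mediators.** A reader might also infer that this is tested nowhere. That is too firm. The mixed-model paragraph names only the three primary outcomes, but the Aims section announces the time-by-group test for several self-report measures, including the primary ones, and calls the mediators secondary outcome variables. The text is ambiguous. Even if that test is run, it does not put Group into the path models.

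**The rates.** The high figures rest on one mediator per model and equal correlation with both outcomes. Several mediators in one model lower them a good deal. The article does not say when the mediator is measured. If it is measured at T1 and relates to the T2 outcome only through the T1 outcome, the rate is about 5% whatever r is. Nor does it say that the arms are pooled; that is inferred from the absence of Group. All this stands, and it is why the size is given as a range.

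**Detail left to the analysis plan.** An article may leave much to an unseen plan. Here it does not: it states which variables are exogenous, mediating and endogenous, and that statement does not match the hypothesis.

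**Importance.** Mediation is secondary, and the article itself concedes that its understanding of mechanisms will be partial because there is no active control. This stands and lowers the priority.

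**Conclusion.** The specification is wrong as written: the path models omit the randomised Group and so cannot test whether the secondary variables mediate the effect of counseling. This follows from the text alone.

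The size depends on assumptions. With no counseling effect, mediation could be declared in about 13% to 92% of trials with one mediator per model, or about 4% to 42% per subscale with six parallel mediators, for mediator-outcome correlations of 0.2 to 0.5. A real pathway through a mediator unrelated to baseline would be detected in about 5% of trials, against about 80% to 99% with Group in the model.

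A reader might go further and conclude that every positive mediation finding would be an artefact. The documents do not support that. Such a finding could be one, if the mediator relates to both the earlier and the later outcome. This is plausible for self-report scales chosen as potentially related to burnout.

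The paragraph should be corrected before analysis. The Time by Group test, the sample size and the efficacy conclusion are unaffected.

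**What to change.** Reword the path-analysis paragraph so that, in both the T2 and the T3 models:

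- Group (PC vs WL) is the exogenous variable;
- the model adjusts for the T1 outcome and the T1 value of the mediator;
- the endpoint is the outcome at T2 or T3, replacing the second T1;
- the time at which the mediator is measured is stated;
- the Group-to-mediator path, the mediator-to-outcome path and the indirect effect with a bootstrap confidence interval are reported.

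Add that the T3 model is interpreted as mediation only if the waiting list is still untreated at T3. The article says the design allows care for all participants but not when the waiting list receives it.

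The cost is one rewritten paragraph and a little analysis time. No data collection changes, because the section Outcomes data collection already has all eight questionnaires completed in both groups at T1, T2 and T3.

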### Participants and sample size

Assuming a medium effect size (Cohen's *d* = 0.50), we estimated with the G^*^Power3 software (Faul et al., 2007) that we need a sample size of 128 participants (i.e., two groups of 64 students) to achieve a power of 0.80 (α = 0.05). Thus, a total of 130 students will be recruited from bachelor's courses at Universitas Mercatorum. Participants are eligible for inclusion according with the following criteria: (a) age > 18 years; (b) clinical levels of academic burnout scores [one standard deviation above the mean MBI-SS total score reported in the validation study by Portoghese et al. (2018)]; (c) attendance of 1^st^ or 2^nd^ year of bachelor course at Universitas Mercatorum; and (d) sufficient knowledge of the Italian language. Additional exclusion criteria aimed at selecting a sufficiently homogeneous group of participants are: (a) previous university degree; (b) other psychiatric diagnoses; (c) other ongoing psychological or psychiatric treatments. Finally, we also excluded (d) attendance of 3^rd^ year of bachelor course, to avoid participants drop-outs due to the course conclusion.

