## Instruments

### Screening instruments

#### Maslach burnout inventory-student survey

The MBI-SS (Schaufeli et al., 1996; Italian adaptation: Portoghese et al., 2018) is a 15-item self-report questionnaire composed of three subscales: Exhaustion (EX; item example “*I feel used up at the end of a day at university*”), Cynicism (CY; item example “*I doubt the significance of my studies*”), and Professional Efficacy (PE; item example “*During class I feel confident that I am effective in getting things done*”). All the items are scored by using a 7-point Likert scale ranging from 0 (=“*never*”) to 6 (=“*always*”). We will use the Italian version of MBI-SS from the study of Portoghese et al. (2018), in which reliability coefficients for each of the subscale scores were 0.86 for EX, 0.82 for CY and 0.77 for PE. The MBI-SS will be used to select students with high levels of academic burnout.

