We will also calculate Reliable Change Index (RCI) and Clinically Significant Change (CSC) (Jacobson and Truax, 1991) for each patient, from pre- to post- treatment and at follow-up. The RCI is computed as a ratio in which the numerator represents the difference between each subject's pretest and post-test outcome scores, while the denominator represents the standard error of the difference between the two test scores. According to Jacobson and Truax (1991), RC indices larger than 1.96 indicate that a significant change has occurred. The CSC is represented by a patient's score moving from the “dysfunctional population” range into the “functional population.” For example, pre-treatment to post-treatment of at least 2 standard deviations from the original mean (Evans et al., 1998). Finally, we will provide grouped percentages (PC vs. WL) for those individuals who reliably improved or had a clinically significant change.

The study is based on substantial evidence that psychological interventions promoting self-awareness, cognitive restructuring, and social support are effective strategies to combat burnout. This provides a strong foundation for the research. The study applies these interventions to the specific case of academic burnout, a field that is promising but still lacks strong evidence from randomized controlled trials. In the present article, we described the research protocol of the first randomized controlled trial to determine the efficacy of an online group psychological intervention specifically designed for university students with high levels of burnout. Moreover, we gave attention to several methodological issues. In line with the empirically supported psychological treatments requirements (Chambless and Hollon, 1998), we propose a between-group design with adequate statistical power, and we clearly specified sample characteristics (defined by standard measures). We also identified a large range of possible primary and secondary outcomes, and we planned the implementation of statistical analyses suitable for the understanding of different levels of effects in the data that will be collected.

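### The by-arm improvement percentages count a crossing into the functional range as clinically significant even when the change is below the plan's own reliable-change threshold

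*Protocol article*

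**What the plan says.** The individual-level analysis is described after the mixed model and the path analyses in the Statistical analysis section of the Protocol article. It has three parts.

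- **Reliable change.** The RCI divides the pre–post difference by its standard error ("the denominator represents the standard error of the difference between the two test scores"), and "RC indices larger than 1.96 indicate that a significant change has occurred".
- **Clinically significant change.** "The CSC is represented by a patient's score moving from the" dysfunctional range to the functional one. One example follows: "pre-treatment to post-treatment of at least 2 standard deviations from the original mean". No reliability condition is attached.
- **Reporting.** "we will provide grouped percentages (PC vs. WL) for those individuals who reliably improved or had a clinically significant change".

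Two other sections bear on the size of the problem. Participants and sample size admits students at "one standard deviation above the mean MBI-SS total score reported in the validation study". The description of the Maslach burnout inventory-student survey (MBI-SS) says "reliability coefficients for each of the subscale scores were 0.86 for EX, 0.82 for CY and 0.77 for PE". No total-score reliability and no numeric boundary for the functional range are given.

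**The concern.** The RCI is there to separate real change from measurement error. Joining it to CSC with *or*, when CSC carries no reliability condition, lets a student qualify without passing that test. A student slightly above the cut-off can cross it on a small fluctuation and be reported as clinically significantly changed.

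This sample may be prone to that. Entry is by a threshold on the MBI-SS, so many students will have scores not far above it. If the functional boundary lies near that threshold, small changes produce crossings.

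The CSC text also allows two rules that behave differently. A move into the functional range can be small, whereas a change of 2 SD is large and would normally be reliable anyway. The reported percentage would then depend on which sentence the analyst follows. What is at stake is the absolute level of the improvement percentages in both arms.

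**Working it through.** **The plan's own figure.** The article states no expected improvement rate. Its one computed figure, 128 participants for *d* = 0.50, power 0.80 and alpha 0.05, is reproduced: a two-sided two-sample t-test needs 63.77, hence 64 per arm, with power 0.801. It does not use the RCI or CSC.

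**Reliable-change threshold.** In SD units, with reliability *r*, the threshold is 1.96 × √(2(1 − *r*)). With the article's subscale reliabilities standing in for the total score:

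- *r* = 0.77: 1.96 × √0.46 = 1.33 SD
- *r* = 0.82: 1.96 × √0.36 = 1.18 SD
- *r* = 0.86: 1.96 × √0.28 = 1.04 SD

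**One student.** Take *r* = 0.82 and suppose the functional cut-off is at +1.0 SD. A student falls from +1.2 to +0.9 SD. The RCI is 0.3 / √0.36 = 0.5, far below 1.96, yet the score has crossed and the student counts.

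**How many students.** The simulation assumes normal scores in normative SD units, true-score variance *r* and error variance 1 − *r*. Students are selected at screening at or above +1 SD, then given independent T1 and T2 readings. A fresh T1 reading matches Outcomes data collection, where the MBI-SS is completed again at T1. Reliability runs from 0.7 to 0.9. A crossing means T1 at or above the cut-off and T2 below it. With no true change:

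| Functional cut-off (assumed) | Counted under *or* | RCI alone | Both required | Crossings that are not reliable |
|---|---|---|---|---|
| Entry threshold, +1 SD | about 12–17% | 2.5% | 1.5–2.0% | 87–88% |
| Midway between normative and sample means | about 8–14% | 2.5% | 1–2% | 85–87% |
| Sample mean minus 2 SD | about 3–4% | 2.5% | 0.3–0.4% | about 76% |
| CSC as a 2-SD change | 2.5% | 2.5% | – | none |

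The last row follows from the threshold formula. A change of 2 normative SD exceeds 1.96 × √(2(1 − *r*)) whenever *r* is above about 0.48. It also holds with the SD of the selected sample: at *r* = 0.77 that SD is 0.73, and 2 × 0.73 = 1.46 exceeds 1.33.

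**Per arm of 65.** With the entry-threshold cut-off, 0.124 × 65 ≈ 8 to 0.171 × 65 ≈ 11 students are counted with no true change, against 0.025 × 65 ≈ 1.6 for RCI alone. At the sample mean minus 2 SD, *or* adds roughly one percentage point to RCI alone, under one student per arm.

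**With a true gain of 0.5 SD** (*r* = 0.77 to 0.86), *or* counts 35–39% and the joint rule 9–12% at the entry cut-off. At the sample mean minus 2 SD the figures are 16–21% and 3–4%.

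**The case against.** Several objections have force.

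- **The sentence may promise two percentages.** It can be read as one figure for reliable improvement and another for CSC. The reliable-change rate would then be visible on its own. This narrows the problem but does not remove it, because the CSC figure would still contain crossings below the threshold.
- **The cut-off is assumed.** The entry threshold sets eligibility, and nothing makes it the CSC boundary. The only number attached to CSC is 2 SD. Read as a change, it adds nobody; read as a cut-off below the sample mean, it adds about one point. This stands, and the size can be given only as a range.
- **Joint rule against *or* overstates the gap.** Reliable-only improvement deserves reporting too, so RCI alone at 2.5% is the fairer baseline. This also stands.
- **The method is defined by citation, and cut-off values are often left to an analysis plan.** Whether the cited procedure itself requires reliable change cannot be settled from this document, and the absence of a numeric cut-off is not the complaint. The article does state how the two indices are joined, and that statement lacks the condition.

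A reader might infer that the improvement result will consist largely of measurement error, or that the rule favours the intervention. The document does not support either. At *r* = 0.82, with a true gain of 0.5 SD, unreliable crossings are 64% of those counted at the entry cut-off but 29% at the sample mean minus 2 SD; with a gain of 1 SD they are 36% and 22%. With no effect, the noise enters both arms alike and creates no expected difference between them.

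**Conclusion.** The point holds as a defect in a stated rule. As written, students whose change fails the plan's own 1.96 criterion are counted as clinically significantly changed, on either reading of the reporting sentence.

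With no true change, the excess over RCI alone runs from nothing (CSC as a 2-SD change), through about one point (sample mean minus 2 SD), to roughly 10 to 15 points (entry threshold: 12.4 − 2.5 = 9.9 and 17.1 − 2.5 = 14.6). These figures rest on normal scores, reliability of 0.7 to 0.9 for a total score whose reliability is not given, and cut-offs chosen for illustration. The 8 to 11 students per arm are therefore the upper end of a range and not a prediction.

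It would go too far to say that the trial's efficacy conclusion is at risk. That rests on the Time by Group mixed model, and no test or sample-size figure uses these percentages. This is a minor to moderate correction to a supplementary, descriptive result.

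**What to change.** Amend the end of the RCI and CSC paragraph to do three things.

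1. State one definition of CSC, saying whether the 2-SD example is a change score or a boundary.
2. Count CSC only when RCI exceeds 1.96 in the favourable direction **and** the score moves from the dysfunctional to the functional range.
3. Report four exclusive categories by arm: reliable and clinically significant; reliable only; crossed but not reliable; neither.

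Keeping the third category loses no information and shows how many crossings lie within measurement error. The change takes a sentence or two and needs no new data. Its cost is that the reported improvement percentages will be less favourable.
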